### Procedure for unblinding if needed {17b}

After the study, participants will be unblinded as to which condition they were allocated and offered a full explanation of the study design, aims, and a description of both conditions. This will be done in writing, with the additional offer to discuss the study at the participant’s request. At this time, participants will also be provided information about existing mental health services and support.

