### Strategies to improve adherence to interventions {11c}

Reminders are sent to participants' mobile phones before and during the two-week programme. Frequent monitoring of participant progress and adherence will be conducted, and participants not completing the programme will be contacted personally by the researcher over email to determine the reason for non-adherence and offer technical support and encouragement if needed.

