### Secondary outcomes

Secondary outcomes will be assessed at time points 1, 2, and 3, including mental well-being and psychological distress. Mental well-being will be measured using the Mental Health Continuum Short Form (MHC-SF) [45]. This has 14 items over three subscales: Emotional Well-being, Social Well-being (eudemonic well-being), and Psychological Well-being. The items are scored on a 6-point Likert scale (0–5), then sum-scored.

The Depression, Anxiety, and Stress Scale (DASS-21) [46] will be used to measure psychological distress. The DASS-21 has 21 items divided over three subscales, including Depression, Anxiety, and Stress. The items are assessed using a 4-point Likert scale (0–3), summed together, and then multiplied by two. This results in 3 subscales as well as a total score.

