### Intervention and control programmes

After finishing the baseline survey and the research materials arrive by post, the participant can access the online programme platform (hosted on Thinkific, an online course-sharing platform) to start the programme. The programme is followed daily for 14 days by logging into Thinkific on their personal phones or computers (see Intervention section for intervention procedure description).

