### Data management {19}

The research team will frequently monitor the completion of survey data for completeness and send reminders to participants to amend incomplete data. The interview will be audio recorded, automatically transcribed using Microsoft Teams, and manually edited to remove identifying information. Transcripts will be sent to participants for approval (member checks). The audio file will be destroyed after the transcription has been approved.

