### Composition of the data monitoring committee, its role and reporting structure {21a}

There is no monitoring committee; the research team conducts the monitoring.

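### Mental health service information is tied to unblinding at an undefined time after the study, so a participant with raised DASS-21 scores at T1 reaches it no earlier than about six weeks after programme start

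*Protocol article*

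**What the plan says.** All references are to the protocol article.

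- **Entry.** Eligibility criteria {10} exclude people in current clinical treatment for a mental health disorder and people who report severe symptoms, with depression, suicidal ideation and severe anxiety as the examples. Both are judged by self-report.
- **Measurement.** Under Secondary outcomes: "The Depression, Anxiety, and Stress Scale (DASS-21) [46] will be used to measure psychological distress". It has depression, anxiety and stress subscales. On timing: "Secondary outcomes will be assessed at time points 1, 2, and 3, including mental well-being and psychological distress".
- **Order of events.** Implementation {16c} assigns participants during the enrolment meeting. Participant timeline {13} sends the baseline survey after that meeting, so the first DASS-21 is completed after randomisation.
- **Checks during the trial.** Data management {19}: "The research team will frequently monitor the completion of survey data for completeness and send reminders to participants to amend incomplete data". Section {11c} adds that "participants not completing the programme will be contacted personally by the researcher over email to determine the reason for non-adherence". Section {21a}: "There is no monitoring committee; the research team conducts the monitoring".
- **Harms.** Section {22} says only that no adverse events or harms are expected.
- **Service information.** Section {17b}, directly after describing the written unblinding once the study is over: "At this time, participants will also be provided information about existing mental health services and support".

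**The concern.** Section {17b} fixes a time for the service information, and it is the latest one available: it comes with unblinding. Nothing in that information depends on knowing the allocation, so the link to unblinding delays it without a stated design reason.

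The time is also undefined. The end of the study could be the participant's own final survey or the close of the whole trial, and the two can lie far apart for people enrolled early.

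The trial asks every participant about depression, anxiety and stress three times, and treats severe depression and anxiety as reasons not to enter. It can therefore expect that some participants will report raised scores along the way. As the article stands, the one protective step it describes comes after all exposure and follow-up. What is at stake is participant safety and a clear procedure. The validity of the primary comparison is not affected.

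**Working it through.** The document states no waiting time, so there is no figure to reproduce. The check is calendar arithmetic on the stated schedule.

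**Inputs**
- Programme length, from Intervention and control programmes: "The programme is followed daily for 14 days by logging into Thinkific on their personal phones or computers".
- Follow-up interval, from the section on the post-survey, follow-up survey and compensation: the final survey is sent 4 weeks after the post-survey, that is 28 days.
- Recruitment, from Trial status: November 2024 to June 2025.

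**Programme start to T3:** 14 + 28 = 42 days, or 42 / 7 = 6 weeks.

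**Wait until the information, if it follows the participant's own T3:** (42 − day on which raised scores or symptoms appear) / 7 weeks, with day 0 as programme start.

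| When they appear | Calculation | Minimum wait |
|---|---|---|
| T1, counted from programme start | (42 − 0) / 7 | 6 weeks |
| Mid-programme, day 7 | (42 − 7) / 7 | 5 weeks |
| T2, day 14 | (42 − 14) / 7 | 4 weeks |
| Mid follow-up, day 28 | (42 − 28) / 7 | 2 weeks |
| T3, day 42 | (42 − 42) / 7 | about none |

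The programme starts only after the baseline survey is finished and the materials have arrived by post. The wait counted from T1 itself is therefore somewhat longer than six weeks. Late survey completion lengthens every row.

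**If it follows the end of the trial instead:** every wait grows. For the earliest participants, November to June is about 7 months, and six further weeks for the last participant add about 1.5, giving roughly 8.5 months. This is conditional on a reading that {17b} neither states nor rules out.

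**Sections side by side.** {10} concerns the state at screening, Secondary outcomes concerns scores from T1 onwards, {19} concerns completeness of surveys, {11c} concerns adherence, {22} expects no harm, and {17b} gives service information at the end. No two of these contradict each other. Read together, they do not say what applies to a raised DASS-21 score between T1 and T3, and they place the service information after that whole interval.

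**The case against.** The strongest reply is that this is a condensed article. Participants receive a detailed information letter and consent sheet ({26a}), and a further letter at screening ({15}). Either could carry support contacts or a distress procedure, and neither is shown. Section {17b} also says what is provided at debriefing. It does not say that the information is withheld before then. This stands, and it limits the point to what the article describes. It does not remove the point: {18a} presents the article as setting out the procedures for all contact with participants, and the only time it gives for service information is the late one.

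Some stronger readings are tempting but not supported:

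- **Anyone who worsens waits at least six weeks.** Six weeks is the minimum only for raised scores already present at T1. For later worsening the minimum is shorter, down to about none at T3.
- **Nobody reads the scores.** The article describes a completeness check. It does not say that scores go unread, and silence in a condensed text does not establish it.
- **The exclusion and the repeated DASS-21 conflict.** Screening on current state and later measuring distress are compatible.
- **The DASS-21 covers every listed exclusion.** The article lists depression, anxiety and stress for it. Suicidal ideation is not listed.
- **Many participants are affected.** The article gives no share with severe scores. Its background figure of more than half concerns mental health concerns in people aged 16 to 25 generally, and cannot be carried over to severe symptoms in a screened sample.
- **Participants who leave early are lost to contact.** Section {18b} asks those who withdraw to complete the remaining surveys where possible, and {17b} is not limited to completers.

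**Conclusion.** The point holds in a limited form. The article ties service information to unblinding, leaves the time undefined and describes no earlier provision. The earliest the information arrives is about six weeks after programme start for a participant with raised scores at T1, and about four weeks after T2 for one whose scores are raised there.

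These figures assume that the debriefing follows the participant's own T3 without delay and that surveys are completed on schedule. They are lower bounds, and larger if the end of the trial is meant. The conclusion also assumes that the information letter gives no support contacts, which cannot be checked here. No number of affected participants can be derived from the document.

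This is a cheap improvement and a clarification. It is not an error that affects the trial's analysis.

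**What to change.** 1. In {17b}, separate the service information from unblinding. Give it in identical words to both arms from enrolment and again with each of the T1, T2 and T3 surveys. If the information letter already does this, say so in {17b}.
2. In {17b}, define the end of the study for unblinding: the participant's own T3 or the close of the trial.
3. Reconcile {10}, Secondary outcomes, {17b}, {19} and {22} on DASS-21 scores reported during the trial. Any score threshold, reviewing role or clinical response is for the sponsor and the ethics committee to decide.

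**Cost.** Text on the enrolment material and survey pages, and one amendment. No new measure or visit is needed. The downside is slightly more help-seeking, in both arms. The document gives no basis for sizing it. Identical wording at identical times reveals nothing about allocation. Because randomisation is in blocks of 2 and 4, a change made part-way through recruitment would reach both arms in about equal numbers.

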## Data collection and management

### Plans for assessment and collection of outcomes {18a}

The collection of outcome data will be done via surveys and semi-structured interviews. Below are detailed explanations for assessment and collection plans for each stage of the study, as well as procedures for all participant contact. The researchers collecting data will be trained PhD candidates and master’s level researchers. All survey data will be collected via the Castor Electronic Data Capture system. All interviews will be conducted and recorded on Microsoft Teams.

### Plans to promote participant retention and complete follow-up {18b}

Participants are informed of their right to leave the study at any time without consequences to themselves. Reasons for withdrawals and timing will be documented. To promote participant retention, we will send reminders to those who stop having poor adherence and ask all withdrawn participants to complete the post and follow-up tests where possible. Participants who withdraw are not replaced if they have completed the pre-survey.

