### Participant timeline {13}

#### Enrollment and baseline

In an enrollment meeting hosted on Microsoft Teams, the researcher will walk the participant through the selected programme components and instructions with a PowerPoint presentation and provide time for questions. As listed in the information sheet, advertisement, and screening survey, the participants will be asked for their postal address so that the login details for the respective programme and the free museum tickets (intervention only) can be sent via post. Participants will set up an account on the Samply Research Application [58] to receive reminders about the study. At the end of the meeting, the researcher will explain that the surveys will be sent to them via email (via Castor). Once the participant has no further questions, the enrollment meeting will finish. The participants will then be sent the baseline survey. The list of baseline questions is provided in the overview in Table 3.

**Table 3 Tab3:** Outcomes and timepoints of assessment

Assessment tools	Baseline T1	Post T2	Follow-up T3

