### Implementation {16c}

The enrollment researchers will assign participants to conditions during the enrollment meeting, after informed consent, using the automatic randomisation sequence generated by Castor.

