## Assignment of interventions: blinding

### Who will be blinded {17a}

Participants are blinded to the allocated condition. Although the information sheet specifies that there are two conditions, it is unclear to participants which is the control and which is the intervention due to the high-quality, credible active control condition. It is not possible in this study to keep the researchers blind, as they are responsible for explaining the programmes during the enrollment meeting.

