## Statistical methods

### Statistical methods for primary and secondary outcomes {20a}

The main analysis will be conducted in two stages. The first is according to the intention-to-treat (ITT) analysis principle [60], with all participants included where possible. This includes dropouts and non-completers of the programmes. Second, we will repeat the analysis Per-Protocol (PP) [60] to gain a clearer picture of the intervention-related effects, excluding non-completers or poor-quality data (see exclusions below). To evaluate whether there are differences between the conditions at the post-test, considering baseline differences, a series of ANCOVAs with the condition as the IV and the post-test as the DV, with baseline scores, sex, and age as covariates will be run on primary and secondary outcomes. To evaluate the long-term effects of the intervention and the control condition, linear mixed models (LMM) will be fitted to predict each outcome variable. The same approach will be applied to evaluate the tertiary outcomes.

For more details, see our pre-registration: osf.io/q8c6u.

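### The no-replacement rule starts at the pre-survey, after randomisation, so people who leave in between may be replaced and drop out of the intention-to-treat analysis

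*Protocol article*

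**What the plan says.** Four parts of the Protocol article bear on this.

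- **Retention {18b}.** "Participants who withdraw are not replaced if they have completed the pre-survey". The same section says that the reasons for and timing of withdrawals are recorded, and that everyone who withdraws is asked for the post and follow-up tests where possible.
- **Order of events.** Under Implementation {16c}, "The enrollment researchers will assign participants to conditions during the enrollment meeting, after informed consent". Under Enrollment and baseline, "the researcher will walk the participant through the selected programme components and instructions with a PowerPoint presentation" in that meeting, and once it is over, "The participants will then be sent the baseline survey". Section {17a} confirms the order: the researchers cannot be blind, "as they are responsible for explaining the programmes during the enrollment meeting".
- **Size.** Trial design {8} gives 114 as the number randomised, about 57 per group.
- **Analysis.** Section {20a} says of the main analysis: "The first is according to the intention-to-treat (ITT) analysis principle [60], with all participants included where possible". It adds: "This includes dropouts and non-completers of the programmes". Section {20c} then excludes from the intention-to-treat analysis participants without pre- and post-data on the outcome concerned. If missingness is judged random, it fills missing outcomes by last observation carried forward.

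**The concern.** The point after which a participant can no longer be replaced should be randomisation. Here it is completion of a survey that comes later. Between the two, the participant has been allocated and has heard what the allocated programme involves, but has not yet reached the point that protects them from replacement.

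Leaving at that step can depend on the programme just described, so the people who complete the pre-survey need not be the comparable groups that randomisation produced. If the 114 is filled with survey completers, the arms look complete although some randomised people are missing from them. An analysis of that set is not intention-to-treat in the sense that section {20a} claims. Participants are not told which programme is the control, but they do not need to know that for their decision to depend on the arm. Knowing the content of their own programme is enough.

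**Working it through.** No formula decides this point; the order of events does.

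1. Consent, then randomisation, in the enrolment meeting ({16c}).
2. The allocated programme is explained in the same meeting (Enrollment and baseline; {17a}).
3. The baseline survey is sent after the meeting (Enrollment and baseline).
4. Replacement is barred from completion of that survey onwards ({18b}).

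Steps 1 and 2 come before step 4, so a window exists. The condition in {18b} has a purpose only if people who leave before the survey may be replaced. Nothing in the article says that such people stay in the intention-to-treat set or count towards the 114.

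**What happens to someone who leaves in the window**

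| Their data | Under {20c} and the {20a} ANCOVA |
|---|---|
| No baseline, no post-test | Excluded; there is no earlier observation to carry forward |
| No baseline, post-test obtained | Excluded if {20c} requires both measurements. If it excludes only people who lack both, the ANCOVA still has no baseline value for them |

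They therefore leave the analysis whether or not anyone replaces them. Replacement adds a second problem: the number randomised no longer equals 114.

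**Counts.** With k replaced early leavers, the number randomised is 114 + k, and the share missing from the analysis for this reason is k / (114 + k). The documents give no k, so the values below are assumptions.

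| k | Randomised | Share missing |
|---|---|---|
| 3 | 117 | 3/117 = 2.6% |
| 6 | 120 | 6/120 = 5.0% |
| 11 | 125 | 11/125 = 8.8% |

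**Effect on the dropout allowance.** Sample size {14} takes 102 × 0.48 = 48.96, so 49 per group. Adding 15% gives 49 × 1.15 = 56.35, so 57 per group and 114 in total. The 102 is taken here as stated. The allowance is 114 − 2 × 49 = 16 people. Without replacement, 3, 6 or 11 early leavers with no usable outcome would leave 13, 10 or 5 of those 16 places for later losses.

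**The case against.** The strongest reply has several parts.

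- **Replacement is inferred.** A reader might take {18b} to say outright that early leavers are replaced. It does not: it states only when replacement is barred. This stands, and the point is worded accordingly.
- **Replacement does not itself create the bias.** A reader might multiply an assumed difference in loss between arms by an assumed outcome difference between leavers and stayers, and set the product against the planned d = 0.35. That product measures attrition whose outcomes are not observed. It is the same whether or not anyone is replaced, and the documents supply neither input. Nor does the article say that a new recruit takes the leaver's place in the same arm; allocation follows the Castor sequence. This stands, so no bias figure is given.
- **The direction is open.** A reader might expect the control arm to lose more people, since the other arm receives a free museum ticket. The advertisement ({15}) describes observation skills on a tourist outing and does not mention art, so the control programme fits it at least as well. The pilot, with only 6 people, judged the two programmes comparable in intensity, credibility and enjoyment. Loss could differ either way or not at all.
- **Nothing is hidden from the record.** Section {18b} documents the reasons for and timing of withdrawal. The loss leaves the analysis, not the trial file.
- **The wording is hedged.** Section {20a} includes everyone only where possible, and {20c} states its exclusion openly. This softens the conflict with the intention-to-treat label but does not remove it, because {20a} names dropouts as included and these dropouts cannot be.
- **Replacement protects power.** It keeps the 15% allowance for later losses. This is true and is the real cost of the change, but that gain does not justify dropping randomised participants from the comparison.

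**Conclusion.** The concern holds in a limited form. The cut-off in {18b} falls after randomisation and after the programme has been explained. By implication it permits replacement of randomised participants, and {20c} removes the same people from the intention-to-treat analysis in any case. Both passages conflict with 114 randomised and with an analysis said to include dropouts.

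The size is unknown because the number leaving in this window is not given; the shares of 2.6% to 8.8% rest on assumed counts of 3 to 11. If nobody leaves between the meeting and the survey, the effect is nil. The conclusion rests on reading the condition in {18b} as permitting earlier replacement. The part concerning {20c} does not need that reading. The documents do not show that replacement has occurred, that one particular arm loses more people, or that the estimate is biased by a given amount. The change is worth making because it is cheap and makes the analysis match its label.

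**What to change.** - **{18b}:** reword to say that no participant is replaced after randomisation and that all randomised participants count towards N = 114.
- **{20c}:** amend at the same time, or the two sections will contradict each other. Define the intention-to-treat set as all randomised participants.
- **Missing baseline:** use the post and follow-up tests that {18b} already requests from everyone who withdraws. A participant with an outcome but no baseline stays in the ANCOVA, for example with the baseline set to the overall mean. Age and sex are also covariates and are collected at the same time point, so they need the same provision. This missingness arises after allocation and may depend on it, so add a sensitivity analysis.
- **Reporting:** show by arm in the participant flow everyone who left between randomisation and the pre-survey. Recruitment began in November 2024, so include anyone already replaced and count them as randomised.

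The cost is a few sentences of protocol text, one sensitivity analysis and one line in the participant flow. The price is slightly fewer analysable participants than replacement would give, drawn from the 16-person allowance.
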